### Strategies to improve adherence to the intervention

Strategies to improve adherence to the intervention include (1) preinitiation site evaluation to ensure that the unit does not already cycle light and that it can achieve the light intensity levels specified within the protocol; (2) intensive site initiation and ongoing educational support programme from the trial co-ordinating centre and site research staff; (3) provision of portable bedside light lux metres and check logs to ensure that nursing staff are aware of lighting conditions and are able to adjust them to meet the specified daytime light intensity; (4) prespecified monitoring of light and noise levels of 24 hours on days 7, 14, 28 and 56 and at 36 weeks PMA; (5) regular monitoring of screening logs and data entry; (6) regular discussion about adherence and compliance issues and sharing of solutions and approaches at site investigator meetings and (7) additional online trial meetings and trial newsletters to sites and participants.

### Relevant concomitant care permitted or prohibited during the trial

Eyemasks may be applied for 24 hours/day in both the intervention (active comparator) and routine care (placebo comparator) group during any period when the infant is receiving phototherapy, in accordance with standards of care. Similarly, earmuffs may be worn for 24 hours/day in infants during high-frequency ventilation where that approach is standard care in that environment. Infants may still participate in the routine practice of afternoon ‘quiet time’ if required. This practice allows the dimming of light for 1–2 hours in the afternoon but does not permit the use of cot-covers, eye-masks or earplugs during this period.

Caffeine therapy will be timed in both study groups to be given with the first morning medications at or as close as possible to 8:00. Postnatal steroid administration, when required, will be timed so that the evening dose is given no later than 18:00 and the morning dose no earlier than 6:00. All other postrandomisation management of study infants is at the discretion of the clinical team.

### Outcomes

#### Primary outcome

Standardised cognitive score on Bayley Scales of Infant and Toddler Development–4th Edition at 24 (22–36) months cPNA.

#### Secondary outcomes

##### In hospital secondary outcomes

Survival to 36 weeks PMA.Indices of growth: weight, length, head circumference, body mass index z scores and growth velocity (also measured at 2, 6 and 12 months cPNA).Duration of hospitalisation to discharge from tertiary hospital and to discharge home.Indicators of respiratory illness includingIncidence of bronchopulmonary dysplasia (BPD) (defined by Jensen *et al*).^32^Severity of BPD (as defined by Jensen *et al* and right shift of the SpO_2_/P_I_O_2_ curve at 36 weeks PMA).^32
33^Requirement for respiratory support as determined by duration of mechanical ventilation, duration of any respiratory support and days of supplemental oxygen.Necrotising enterocolitis (NEC) Stage II or greater according to modified Bell’s Criteria.^34^Severe retinopathy of prematurity (ROP) stage III or more, or ROP Stage II plus as defined in the International Classification of ROP 3.^35^Neurologic injury as defined byGrade 3 or 4 intraventricular haemorrhage (IVH).^36^Presence of periventricular leukomalacia.Number of confirmed blood culture positive episodes of sepsis.

##### Key long-term secondary outcomes at 24 (22–36) months cPNA

Survival, censored at 24 months cPNA.Proportion of scores >1 SD and >2 SD below mean for cognitive composite score on Bayley-4.Individual composite subscores for language, motor and social-emotional subscales of the Bayley-4.Neurobehaviour using the Infant Toddler Social-Emotional Assessment.^37^Social communication using the Communication and Symbolic Behaviour Scales Infant-Toddler Checklist (CSBS-ITC).^38^Measures of growth: weight, height, body mass index, growth velocity.

##### Additional secondary outcomes to be reported in substudies

Risk of neuromotor disorder from assessments of the General Movements Assessment at 36 weeks PMA, and 3 m and 3.5 m cPNA.Maternal–infant attachment using the Maternal Postnatal Attachment Scale at 2, 6 and 12 months cPNA.^39^Primary caregiver mental well-being at 2, 6, 12 and 24 months cPNAAnxiety score using the Generalised Anxiety Disorder-7.^40^Depression using the Edinburgh Postnatal Depression Scale (2, 6 and 12 months)^41^ or the Centre for Epidemiologic Studies Depression Scale Revised at 24 months cPNA.^42^Measures of sleep defined by actigraphy including total average time asleep/24 hours at 36 weeks PMA, and 2 months and 6 months cPNA for the infant and at 2 months and 6 months for the primary caregiver.Time to onset of circadian rhythms measured by salivary melatonin and cortisol at day 7, 14, 28 and at 36 weeks PMA during hospitalisation.Score on Toddler module of the Autism Diagnostic Observation Schedule (ADOS) Second Edition at 24 months cPNA.

##### Planning for long-term outcomes beyond the primary study endpoint

Long-term outcomes will include assessment of health service utilisation and medications where parents have provided us with consent to obtain this information.

### Cost-effectiveness analysis

Economic evaluation will ascertain the cost-effectiveness of cycledlight and noise compared with routine non-cycled environmental care over the first 2 years of life and will include estimation of long-term outcomes. Net savings will be estimated by comparing the length of stay with the costs of the intervention. The intervention cost, at a single primary recruiting site, will be assessed by prospective resource unit tracking including materials and time required for application/removal of eye-masks and noise protection. Resources will be costed using standard sources. Effectiveness over the longer-term will comprise evaluations of health-service utilisation.

### Adverse events

Adverse events during the intervention period will be assessed from randomisation until death or discharge home from hospital, or 44 weeks PMA, whichever occurs soonest.

The 2016 recommendations of the National Health and Medical Research Council for safety reporting^43^ will be followed by the CIRCA DIEM trial.

Study related adverse events during the intervention period will include

ROP with a stage III or greater, or stage II with Plus disease on International Classification of Reinopathy of Prematurity Third Edition.Skin damage from use of wearables.Any perceived safety issue associated with the intervention devices.

Study related serious adverse events during the intervention period will include

Death before discharge home from hospital deemed potentially associated with the intervention.Any perceived life-threatening event during hospitalisation associated with the intervention devices.

Study-related serious adverse events occurring following the intervention period will include death after discharge and before 2 years of age associated with the intervention.

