#### Intervention description

##### Light

For the intervention group, the CIRCA DIEM Study will target cycled light from 0 lux at night to a range of 300-600 lux during daytime as this level was defined as safe for preterm infants.^26^ We thus anticipate a minimum separation of 200 lux between the intervention group and comparator group for daytime light exposure,^30^ and a 300 lux difference between daytime/night-time light intensity for the intervention group to ensure adequate light stimulus for entrainment of the endogenous circadian rhythm. The intervention will commence as soon as possible after randomisation and continue until discharge home or (for infants hospitalised for longer than 8 weeks) for a minimum of 8 weeks after commencement of the intervention.

Conversely, the CIRCA DIEM Study will use a pragmatic definition of non-cycled light environment for the comparator group as a difference between daytime and evening light intensity that does not exceed 100 lux.

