#### Reporting of adverse events and assessing their relatedness (causality) to trial interventions

The site principal investigator is responsible for reporting all predefined adverse events and serious adverse events from time of study enrolment to hospital discharge to the Trial Coordinating Centre, and grading the causality of these events as unrelated, possible, definite in relation to their causality with respect to the use of the study intervention. The aim will be that such reporting is achieved within 24 hours of the site investigator becoming aware of the event. All intervention-related SAE will be reviewed by the Data Safety and Monitoring Committee (DSMC) with the goal of providing a blinded report to the Chair of the Trial Steering Committee within 2 weeks of the review. The DSMC will additionally consider the composite outcome of mortality before discharge or severe IVH (grade 3 or 4 IVH), or NEC (stage IIA or higher) or ROP requiring treatment, in consideration of the safety of the intervention.

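### Adverse-event assessment can close at 44 weeks PMA while site reporting and device use run on to discharge, and no site duty covers the post-discharge deaths defined as serious adverse events

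*Protocol article*

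**What the plan says.** Four places in the protocol article bear on this.

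- **Adverse events, opening sentence.** The window is given in these words: "assessed from randomisation until death or discharge home from hospital, or 44 weeks PMA, whichever occurs soonest".
- **Adverse events, lists.** Non-serious study-related events include skin damage from the devices and any perceived safety issue with them. The serious events listed for the intervention period are of two kinds. One is a death: "Death before discharge home from hospital deemed potentially associated with the intervention". The other is a life-threatening event in hospital linked to the devices. For the time after the intervention period one serious event is listed, "death after discharge and before 2 years of age associated with the intervention", which covers death only.
- **Section on reporting and causality.** The duty placed on each site's lead investigator is stated as "reporting all predefined adverse events and serious adverse events from time of study enrolment to hospital discharge". The same person judges whether each event is related to the intervention. The DSMC reviews all intervention-related serious events. It also considers a composite that includes mortality before discharge.
- **Light (Intervention description) and the criteria for discontinuing or modifying the intervention.** The intervention is to "continue until discharge home or (for infants hospitalised for longer than 8 weeks) for a minimum of 8 weeks after commencement of the intervention". Early stopping is allowed in two situations: discharge to a non-participating regional unit after at least 8 weeks of intervention, or transfer to another ward for long-term care once 40 weeks PMA is reached. Stopping outside these is a protocol deviation.

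**The concern.** The two safety sections give different end points for the same events. One stops at 44 weeks PMA if the infant is still in hospital, and the other goes on to hospital discharge. Device use has no PMA ceiling, so the shorter window can shut while an infant is still wearing the eye mask and ear plugs at night. The infants concerned are those with the longest stays.

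The harms most directly tied to wearing time, skin damage and perceived device problems, are the ones with nothing behind them if assessment stops. A further gap concerns deaths after discharge: the plan defines a serious event, but the reporting sentence ends before that event can occur. The Discussion makes uptake conditional on efficacy without severe adverse effects, so safety events should be ascertained by one rule in all infants.

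**Working it through.** No sample size, power or alpha figure is involved, so there is no stated figure to reproduce. The check compares the windows and adds timeline arithmetic.

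**1. The windows side by side**

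| Item | Starts | Ends | PMA cap |
|---|---|---|---|
| Event assessment (Adverse events) | randomisation | earliest of death, discharge home, 44 weeks PMA | 44 weeks |
| Site reporting (Reporting of adverse events) | enrolment | hospital discharge | none |
| Serious event: related death in hospital | intervention period (list heading) | discharge home | none in the item |
| Serious event: life-threatening event | intervention period (list heading) | end of hospitalisation | none in the item |
| Serious event: related death afterwards | discharge | 2 years of age | not applicable |
| Device use (Light; discontinuation criteria) | soon after randomisation | discharge home, subject to the 8-week wording and the two stopping situations | none |

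Rows 1 and 2 disagree for any infant in hospital after 44 weeks PMA. Row 1 can also end before row 6.

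**2. Does the 8-week minimum itself run past 44 weeks PMA?**

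Inputs: gestation strata and consent windows from Inclusion criteria (168 hours below 28 weeks; 72 hours from 28 to below 32 weeks), and the 8 weeks from Light. Assumption: the intervention starts within the consent window.

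Latest end of the minimum = upper gestation limit + consent window + 8 weeks.

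- Below 28 weeks: 28 + 168/(24 × 7) + 8 = 28 + 1 + 8 = 37.0 weeks PMA, which is 44 − 37.0 = 7.0 weeks before the cap.
- 28 to below 32 weeks: 32 + 72/(24 × 7) + 8 = 32 + 0.43 + 8 = 40.4 weeks PMA, which is 3.6 weeks before the cap.

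So the minimum never outlasts the assessment window. The mismatch arises only because use may continue to discharge home. It needs a stay beyond 44 − 32 = 12 weeks after birth at 32 weeks, or 44 − 28 = 16 weeks after birth at 28 weeks.

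**3. How many infants?**

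The documents give no frequency. As an assumed range, 0.5% to 5% of the 868 planned infants (Sample size):

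- 0.005 × 868 = 4.3 and 0.05 × 868 = 43.4, so about 4 to 43 infants in all.
- 0.005 × 434 = 2.2 and 0.05 × 434 = 21.7, so about 2 to 22 in the group that wears the devices, if all of them were still wearing them.

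**4. Which events have another route to the safety committee or the results?**

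- Death in hospital: a listed serious event, reportable to discharge, and part of the DSMC composite.
- Any death to 24 months corrected age: counted in the survival outcome (Key long-term secondary outcomes).
- Retinopathy: severe disease is an in-hospital secondary outcome, and disease requiring treatment is in the DSMC composite.
- Skin damage and perceived device safety issues: in neither the DSMC composite nor the listed secondary outcomes.

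**5. Class of a related in-hospital death after 44 weeks PMA**

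The in-hospital class is headed as belonging to the intervention period. If that period is taken from the Light section, it is still open while the devices are in use, and the death fits. If it is taken from the opening sentence of Adverse events, it closed at 44 weeks, and the later class begins only after discharge. The text supports either reading.

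**6. Deaths after discharge**

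The definition runs from discharge to 2 years of age. The sentence that gives the site its reporting and causality duty ends at hospital discharge. The survival outcome will show that a death occurred but not whether it was graded as related, and the DSMC's review of serious events is limited to those that are intervention-related.

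**The case against.** A reader might infer that late in-hospital deaths escape safety reporting altogether. The documents do not support that. A potentially related death before discharge home is a listed serious event with no PMA cap in its own wording, the site must report to hospital discharge, and the DSMC composite counts mortality before discharge. What is left is an ambiguous heading.

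A reader might also take the 2-year limit as a third window that contradicts the other two. It does not: it is a separate category, for death only, after the intervention period. Nor does it cover every death after discharge, only those associated with the intervention.

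The strongest remaining objections are these.

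- The 8-week wording in Light can be read as letting long-stay infants stop well before 44 weeks, and stopping is permitted from 40 weeks PMA on transfer to another ward. This stands in part. It makes the affected group smaller, but eight weeks is given as a minimum, and the discontinuation criteria treat other stopping as a deviation.
- Sites work from the full protocol and its forms, which are not shown, so different collection between sites is not demonstrated. This stands. The article shows conflicting rules, not that sites have acted on them differently.
- Who reports a death after discharge is operational detail that an article may leave out. This stands only in part, because the article does not stay silent: it states the duty and ends it at hospital discharge.

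**Conclusion.** The point holds as a conflict between stated rules. Under the Adverse events section, assessment stops at 44 weeks PMA for an infant still in hospital. Under the reporting section it continues to hospital discharge, and nothing requires the devices to be off by 44 weeks. The practical loss, if the shorter window is applied, is non-serious device events in infants still in hospital and on the devices after 44 weeks PMA. That group is probably small; the 4 to 43 infants above rest entirely on an assumed 0.5% to 5%.

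Two lesser defects go with it. The class of a related in-hospital death after 44 weeks is ambiguous, though the death is still reportable and counted. The reporting and causality duty does not reach the post-discharge deaths that the plan defines as serious adverse events. In addition, the reporting section does not say whether hospital discharge means leaving the tertiary hospital or going home, which the in-hospital secondary outcomes treat as separate events.

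There is no effect on the primary outcome, sample size, power or alpha. The change is worth making because it improves safety ascertainment at little cost, and follow-up for deaths is still running: the article expects primary outcome data collection to end in early 2029.

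**What to change.** - Reconcile Light, the discontinuation criteria, Adverse events, and the reporting and causality section to one stated safety window, with one start point, that covers all time on the devices. Where that window ends is for the sponsor to settle.
- Define the intervention period once and use it in the headings of the serious event lists, so that no in-hospital death falls between the two classes.
- State whether hospital discharge in the reporting section means discharge home.
- Extend the site's reporting and causality-grading duty to the post-discharge deaths up to 2 years of age that the Adverse events section defines as serious.

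The cost is a wording amendment and a few more event forms. Survival is already followed to 24 months corrected age, so the deaths themselves need no new data collection, only a causality grading and a route to the DSMC.

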#### Reporting of adverse events and assessing their relatedness (causality) to trial interventions

The site principal investigator is responsible for reporting all predefined adverse events and serious adverse events from time of study enrolment to hospital discharge to the Trial Coordinating Centre, and grading the causality of these events as unrelated, possible, definite in relation to their causality with respect to the use of the study intervention. The aim will be that such reporting is achieved within 24 hours of the site investigator becoming aware of the event. All intervention-related SAE will be reviewed by the Data Safety and Monitoring Committee (DSMC) with the goal of providing a blinded report to the Chair of the Trial Steering Committee within 2 weeks of the review. The DSMC will additionally consider the composite outcome of mortality before discharge or severe IVH (grade 3 or 4 IVH), or NEC (stage IIA or higher) or ROP requiring treatment, in consideration of the safety of the intervention.

### Participant timeline

The flow chart for the study intervention is shown in figure 1. A schedule of enrolment, assessments and visits are shown in online supplemental table S1.

### Sample size

The initial sample size for the CIRCA DIEM study planned to recruit up to 954 babies to have over 90% power to detect a meaningful change in cognitive score of 4 points, which we defined as the lowest difference considered sufficient to promote a change in clinical care. A sample size re-estimation was planned at 75% completion of recruitment.

Sample size is based on a median difference of 4 points in the primary outcome (standardised cognitive score on the Bayley-4). The standardised score for cognition on Bayley-4 in the general population is designed to have a mean of 100 with an SD of 15.^29^ However, asymmetric distributions may be observed in the trial population. A planned sample size re-estimation was performed after 75% participants had been recruited, using simulation in the sim.ssize.wilcox.test function from the MKpower package.^44^ With the revised sample size of 624 (312 in each group), the study has 90% power to detect an absolute median difference in standardised cognitive score on Bayley-4 of at least 4 points, assuming a score of 85 (corresponding to –1 SD) and SD of 15 in the control group. The CIRCA DIEM study will recruit at least 868 infants (434 in each group) to allow for an anticipated 10% loss to follow-up (LTFU), and an incidence of multiple birth of 20%.

### Recruitment

Centres with a positive research culture, capacity to achieve the trial intervention and a clearly stated position on equipoise for the research question are included as primary study sites. Co-recruitment to other studies conducted in parallel is permitted to address issues of feasibility of recruitment targets in this highly powered trial within an in-demand finite population of very preterm and extremely preterm infants.

### Randomisation

#### Sequence generation

Computer-generated randomisation tables were developed and uploaded by the study biostatistician ([name]) from The Kids Research Institute Australia (The Kids), Perth Australia. Treatment allocations were generated using random permuted block sizes, stratified by study centre and gestational age (<28 weeks’ PMA vs 28.0 to <32.0 weeks’ gestation), maintaining 1:1 randomisation of infants to each study group.

#### Allocation concealment mechanisms

Infants are randomised to intervention or standard care via the concealed randomisation facility built into a web-based study Research Electronic Data Capture (REDCap, Vanderbilt University) database.^45^ Individuals performing randomisation will be unable to access the randomisation sequence. The REDCap database uses a checklist to confirm eligibility prior to randomisation.

#### Implementation

Research staff can screen for infants and approach families for informed consent antenatally or postnatally in the first 7 days (168 hours) for infants in Strata 1 (<28 weeks’ PMA) or in the first 72 hours for infants in Strata 2 (28.0 to <32.0 weeks’ PMA). Infants are randomised to either intervention (cycled light and noise) or routine environmental care

For multiple births, the first infant will be randomised and second and subsequent siblings from the same pregnancy will be allocated to the same group as the randomised first sibling. This approach is used to avoid any confounding from conflicting sibling sleep schedules that may impact on the primary outcome if the intervention alters sleeping behaviours with an effect extending beyond the initial period of hospitalisation.

